#### Secondary Outcome Measure

The secondary outcome measure is changes in the Menorrhagia Impact Questionnaire (MIQ) [13], evaluated at baseline, the end of intervention period, and follow-up visits.

#### Safety Outcomes

The safety of the trial intervention will be evaluated by recording the incidence of adverse events on every scheduled follow-up visit. All adverse events during the study timeline will be recorded and monitored per the Good Clinical Practice Guidelines. The investigator will report the same to the institutional ethics committee and the sponsors at the earliest opportunity. To assess the safety, hematological and biochemical investigations such as complete blood count and liver and kidney function tests will be done at baseline and the end of the intervention period.

### Sample Size

To calculate the sample size, we anticipated a difference of 70 units in average PBAC score after treatment between the two groups (*Trinakantamani*
*pishti* along with *Ashokarishta* vs tranexamic acid tablet), with an SD of 137 units based on the results of the previous study [14]. With 95% confidence level (α=.05) and 80% power, the number of patients to be enrolled in the study was calculated using the following formula:

where *Z*_1 – α/2_=1.96, *Z*_1 – β_=0.84, σ=137, and δ=70.

Expecting a dropout rate of 15%, the number of patients is estimated to be 60 + 9 = 69. Thus, approximately 70 patients should be enrolled in each group.

### Randomization and Allocation

A randomization chart will be generated with the help of computer-generated random numbers. Participants will be randomized in a ratio of 1:1 to either of the two groups. The randomization schedule will be strictly controlled and remain with the biostatistician/data analyst. Sequentially numbered, sealed, opaque envelopes will be used to conceal the allocation.

### Study Procedure

The participants will be screened for menorrhagia as per the inclusion criteria. Prior to any trial-related activity, the investigator will give the verbal information and written information in a printed form about the trial to the participant, parents, or guardians to read and understand. The investigator would ensure that the participants are fully informed about the aims, procedures, discomforts, and expected benefits of the trial. It must be emphasized that participation is voluntary, and participants have the right to discontinue the trial at any time without any prejudice. A voluntary, signed informed consent will be obtained from the participants prior to any clinical trial–related procedure.

After the screening, if the participants are found to be suitable, then they shall be enrolled in the study after signing the consent form. The required investigations will be carried out, and subsequently, within one week or as soon as laboratory values are received and found to be within permissible limits, the participants will be enrolled in the study, and that day will be considered visit 1 or the baseline visit. The treatment will be given to the participants after fulfilling all the formalities as per the protocol. The subsequent follow-ups will be on the 30th day (visit 2), the 60th day (visit 3), the 90th day (visit 4), the 120th day (visit 5), and the 150th day (visit 6; ie, completion of active treatment). Participants will visit the study site 6 times during the trial. The details of the activity during each visit are presented in Table 2 and Figure 1.

**Table 2 table2:** Study schedule.

Components	Screening	Baseline (visit 1)	30th day (visit 2)	60th day (visit 3)	90th day (visit 4)	120th day (visit 5)	150th day (visit 6)
Informed consent	✓						
Demographics and medical history		✓					
Laboratory investigations	✓		✓		✓		
Assessment of clinical signs and symptoms		✓	✓	✓	✓	✓	✓
Assessment of the MIQ^a^		✓	✓	✓	✓	✓	✓
Clinical examination	✓						
Assessment of the PBAC^b^		✓	✓	✓	✓	✓	✓
Assessment of ADRs^c^			✓	✓	✓		
Assessment of drug compliance			✓	✓	✓		
Issue of trial drugs every 20 or 30 days							

^a^MIQ: Menorrhagia Impact Questionnaire.

^b^PBAC: Pictorial Blood Loss Assessment Chart.

^c^ADR: adverse drug reaction.

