### Outcome Measures

#### Primary Outcome Measures

Primary outcome measures are changes in the amount of uterine bleeding evaluated by the PBAC, changes in the duration of bleeding, and the attainment of a normal amount of blood loss during the interval of cycles, evaluated at baseline, the end of every cycle up to 3 cycles, and follow-up visits.

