### Timelines With Deliverables

The total study period spans 36 months and is divided into four distinct phases. During the initial phase, which lasts from months 1 to 6, efforts will focus on procuring standard trial drugs and finalizing laboratory arrangements. Additionally, tasks such as staff recruitment, equipment procurement, and finalization of case report forms (CRFs) will be undertaken. The second phase, covering months 7 to 23, will be dedicated to the recruitment of participants for the study. Subsequently, months 24 to 34 will constitute the treatment period, during which participants will undergo interventions as per the study protocol, with follow-up assessments conducted accordingly. Finally, in the last phase spanning months 35 to 36, data compilation, analysis, report preparation, and publication will be the primary activities, culminating in the dissemination of study findings.

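### Change in PBAC and in bleeding duration are primary outcomes, but the schedule leaves no reliable room to chart an untreated menses before visit 1, so the conclusion should rest on the between-arm post-treatment comparison

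*Protocol article*

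**What the plan says.** Under Primary Outcome Measures, the protocol article names "changes in the amount of uterine bleeding evaluated by the PBAC, changes in the duration of bleeding" and attainment of a normal amount of blood loss. These are assessed at baseline, at the end of each of three cycles, and at follow-up visits.

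Study Procedure puts consent before everything else: "A voluntary, signed informed consent will be obtained from the participants prior to any clinical trial–related procedure". Investigations follow, and then "within one week or as soon as laboratory values are received and found to be within permissible limits, the participants will be enrolled". Of the enrolment day it says "that day will be considered visit 1 or the baseline visit". Treatment is given once the formalities are complete.

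Table 2 has a screening column. The PBAC row is blank there and is ticked from visit 1 through visit 6. Duration of bleeding has no row of its own, so its baseline assessment rests on the outcome section.

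Inclusion Criteria ask for regular cycles of 21-35 days with heavy loss, defined subjectively or by a PBAC above 100, or bleeding beyond 7 days, over three consecutive cycles.

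Sample Size is built on "a difference of 70 units in average PBAC score after treatment between the two groups", with an SD of 137. Statistical Methods plans paired tests within groups and independent-sample tests between groups, with nonparametric counterparts.

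**The concern.** A PBAC total and a bleeding duration each describe one complete menses. The event that triggers visit 1 is the return of laboratory results, not the end of a menses. A chart handed out by the trial cannot start before consent, and there may be only about a week from then to visit 1. Most women will not begin and finish a menses in that time. The later assessments come about 30 days apart, so whole menses can be charted between them.

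The baseline may therefore be of poorer quality than the values it is subtracted from. Two things are at stake. Error in the baseline enters every change score and can weaken the comparison between arms. The within-group paired tests are also exposed: if the before and after values were obtained differently, part of the change reflects the way of measuring. A baseline recalled as heavier than it was would look like improvement in both arms, and a part-menses score at visit 1 would do the opposite.

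**Working it through.** **1. The plan's own sample size.** Inputs from Sample Size: Z values 1.96 and 0.84, SD 137, difference 70.

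n = 2 × ((1.96 + 0.84) × 137 / 70)² = 2 × 5.48² = 60.06, so 60 per group as stated.

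Power at 60 per group = Φ(70 / (137 × √(2/60)) − 1.96) = Φ(2.80 − 1.96) = 79.9%. This refers to the PBAC score after treatment and does not involve the baseline.

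**2. Chance that a complete menses falls between consent and visit 1.** Inputs: cycle length C of 21-35 days and the route for bleeding beyond 7 days (Inclusion Criteria); a nominal gap W of 7 days (Study Procedure). Assumptions: consent falls at a random point in the cycle; a 5-day menses and a 14-day laboratory wait are illustrative. For a menses of D days:

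- continuous time: max(0, W − D) / C
- counting whole days: max(0, W − D + 1) / C

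| Gap W | Menses D | Continuous, C = 21 / 28 / 35 | Whole days, C = 21 / 28 / 35 |
|---|---|---|---|
| 7 | 5 | 9.5 / 7.1 / 5.7% | 14.3 / 10.7 / 8.6% |
| 7 | 7 | 0 / 0 / 0% | 4.8 / 3.6 / 2.9% |
| 7 | 8 or more | 0 / 0 / 0% | 0 / 0 / 0% |
| 14 | 8 | 28.6 / 21.4 / 17.1% | 33.3 / 25.0 / 20.0% |

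A window certain to contain one complete menses is about C + D days. For an 8-day bleed that is 29 days (C = 21) to 43 days (C = 35).

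**3. Effect of a poor baseline on the comparison between arms.** Assume SD 137 at both times, 60 per arm, and a baseline-to-follow-up correlation r, which the article does not give.

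- SD of change = 137 × √(2(1 − r))
- residual SD with baseline as covariate = 137 × √(1 − r²)
- power = Φ(70 / (SD × √(2/60)) − 1.96)

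| r | SD of change | Power, change score | Power, post-treatment score | Power, post-treatment with baseline covariate |
|---|---|---|---|---|
| 0.2 | 173.3 | 60% | 79.9% | 81.5% |
| 0.3 | 162.1 | 66% | 79.9% | 83.5% |
| 0.5 | 137.0 | 80% | 79.9% | 89.8% |
| 0.7 | 106.1 | 95% | 79.9% | 97.5% |

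The change score matches the planned power only when r is about 0.5 or higher. Error in the baseline pushes r down, by an amount the article gives no means to estimate. The covariate-adjusted comparison is never below the planned power in this range.

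**The case against.** A reader might infer that almost no woman has a charted untreated menses, and that change will in practice be a recalled score subtracted from charted ones. The article does not support that. A PBAC above 100 is one entry route and the criteria look back over three cycles, so some women may arrive with a chart kept before consent, which visit 1 would simply record. The article does not say which menses supplies the baseline or how it is recorded; the full protocol or CRF may. Table 2 uses the same row for visits 1 to 6, and nothing states that later scores are charted differently. What stands is narrower: neither the subjective nor the prolonged-bleeding route requires an earlier chart, and the printed schedule does not provide for one.

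A reader might also take one week as a fixed limit and conclude that at least 90% lack a charted menses. The text allows visit 1 to wait for laboratory results, and a longer wait raises the share with a complete menses, as the 14-day rows show.

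A third inference would be that the randomised comparison is biased. In expectation it is not, provided baseline is recorded before allocation is known, because baseline then precedes treatment in the same way in both arms. The article does not state that order, and the trial is open-label. The third primary outcome, attaining normal loss, also needs no charted baseline.

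Finally, the power loss depends on analysing unadjusted change with a low correlation. At 0.7 the change score does better than planned, and the sample size already refers to the post-treatment score. All of this is right, and it points to the analysis remedy.

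**Conclusion.** The point holds in this form. The schedule fixes baseline by laboratory turnaround, with no PBAC at screening and no untreated observation cycle, while two primary outcomes are changes in whole-menses measures. A trial-issued chart cannot reliably supply that baseline: for a 7-day gap it captures a complete menses in 0% of women bleeding more than 7 days and about 6-14% of those bleeding 5 days; for an assumed 14-day gap, 17-33% of those bleeding 8 days. These figures assume a random point in the cycle and apply only to charts issued at consent.

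The consequence is noise rather than bias between arms, on the condition about allocation given above. Change-score power is 60% to 95% for assumed correlations of 0.2 to 0.7, against 79.9% for the post-treatment score whatever the correlation. The within-group paired tests are the weakest part: being uncontrolled, they would not establish efficacy even with a good baseline, and an uncertain one makes them less reliable still.

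**What to change.** **Analysis.** Make the primary comparison for PBAC and for duration the between-arm difference in the post-treatment value, with the baseline value as a covariate. For PBAC this is the quantity the sample size is built on. Report within-group change descriptively, without offering its paired tests as evidence of efficacy.

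**Recording.** Add a CRF item stating whether each baseline was charted or recalled, and which menses it describes. Record also whether it was obtained before allocation was known, since the absence of bias depends on that.

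**Women still to be enrolled.** Issue the chart at consent, so that any menses completed before visit 1 is charted. This should not be made a condition that delays treatment. Guaranteeing a full charted menses could take about 29-43 days for an 8-day bleed, would let the screening laboratory values grow old, and would split the baseline definition in a trial with 79 of 140 women (56%) enrolled by December 2024.

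**Cost.** A small change to the analysis wording and the CRF, plus earlier issue of a chart already in use. The change-from-baseline result becomes less prominent, and women already enrolled can only be classified by how their baseline was obtained.

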### Eligibility Criteria

#### Inclusion Criteria

Participants will include those aged 20-50 years with menorrhagia—that is, regular (21-35 days) cycle with HMB loss, subjectively or objectively defined (Pictorial Blood Assessment Chart [PBAC] score of more than 100 points) [12], or prolonged bleeding (bleeding more than >7 days) for 3 consecutive cycles—who are willing and able to participate in the study.

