### Study Interventions (Investigational Products)

Participants in the treatment group will receive 250 mg of *Trinakantamani*
*pishti* twice a day orally before meals, 20 mL of *Ashokarishta* twice a day orally before meals, and 1 iron and folic acid tablet (100 mg of elemental iron and 1.5 mg of folic acid) twice a day orally after meals for 3 months. The treatment group’s medicines (investigational products) will be procured from Good Manufacturing Practices–certified pharmacies, namely, Indian Medicines Pharmaceutical Corporation Ltd. and Central Ayurveda Research Institute, along with the Certificate of Analysis to ensure the quality and safety of the medicines. The study drugs will be kept in a secure place and will only be supplied to the participants under the guidance of the investigator. A record will be maintained for the drug dispensed. Any discrepancies between amounts dispensed and returned will be explained.

Participants in the control group will receive a 500-mg tranexamic acid tablet thrice a day for 7 days from the first day of menses for 3 cycles and 1 iron and folic acid tablet twice a day orally for 3 months.

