### Data Safety and Monitoring

The safety of the trial intervention will be evaluated by recording the incidence of adverse events on every scheduled follow-up visit. All adverse events during the study timeline will be recorded and monitored per the International Council for Harmonization of Technical Requirements for Pharmaceuticals for Human Use’s Guideline for Good Clinical Practice. The investigator will report the same to the institutional ethics committee and the sponsors as soon as possible.

For facilitating appropriate reference standards for scientific, ethical, and safety issues before the trial begins, this protocol has been developed according to the 2013 SPIRIT (Standard Protocol Items: Recommendations for Interventional Trials) and CONSORT (Consolidated Standards of Reporting Trials) statements [15].

After completion of the study on 25% of the total participants, the data will be analyzed for the safety of the trial drugs. The project monitoring committee will monitor the trial’s progress through review meetings and site visits as per the requirement to ensure strict adherence to the trial protocol and correct completion of the CRF.

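### Table 2 stops scheduled adverse-reaction assessment at day 90, while the safety text requires adverse events to be recorded at all five follow-up visits, to day 150

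*Protocol article*

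**What the plan says.** The safety text of the protocol article sets a broad duty. Safety Outcomes states: "The safety of the trial intervention will be evaluated by recording the incidence of adverse events on every scheduled follow-up visit". Data Safety and Monitoring repeats this and adds: "All adverse events during the study timeline will be recorded and monitored".

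Study Procedure lists the visits: "The subsequent follow-ups will be on the 30th day (visit 2), the 60th day (visit 3), the 90th day (visit 4), the 120th day". Day 120 is numbered as the fifth visit, and the list ends with "the 150th day (visit 6; ie, completion of active treatment". That makes five follow-up visits after baseline. The same section refers the reader to Table 2 and Figure 1 for what is done at each visit (Figure 1 is not available to this review).

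In Table 2, the row "Assessment of ADRs^c" has ticks at visits 2, 3 and 4 only. The rows for signs and symptoms, the MIQ and the PBAC are ticked through visit 6. No other row covers adverse events.

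Two further statements bear on when treatment ends. The control group receives a "500-mg tranexamic acid tablet thrice a day for 7 days from the first day of menses for 3 cycles", and the inclusion criteria admit women with a "regular (21-35 days) cycle with HMB loss". The treatment group's products are given for 3 months, and the Laboratory Tests section places the end of treatment at day 90.

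**The concern.** Safety is a stated outcome, and the document gives two incompatible instructions for collecting it. Under the text, adverse events are sought at five visits over 150 days. Under the table, they are sought at three visits over 90 days, which leaves the last 60 days without a scheduled assessment.

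The cut-off may also treat the two groups differently. One regimen is fixed by calendar time and the other by menstrual cycles. For some women the third tranexamic acid course could finish, or even start, after the last scheduled assessment, while treatment-group dosing would be over at about that visit. A comparison of adverse-event incidence by arm would then rest on unequal coverage of treated time. Both groups would also lose systematic assessment after treatment.

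**Working it through.** **Step 1: text against table.** No plan figure needs reproducing here; the check is a count.

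- Follow-up visits named in Study Procedure: days 30, 60, 90, 120, 150, so 5.
- Visits where the safety text requires recording: all scheduled follow-up visits, so 5.
- Visits where Table 2 ticks adverse-reaction assessment: days 30, 60, 90, so 3.
- Shortfall: 5 − 3 = 2 visits (days 120 and 150), covering 150 − 90 = 60 days.

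**Step 2: can tranexamic acid dosing pass day 90?** Inputs:

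- Cycle length L, 21 to 35 days (Inclusion Criteria).
- Three 7-day courses, each starting on the first day of menses (Study Interventions).
- U, the number of days from visit 1 to the first on-study menses, between 0 and L. The document does not say where in the cycle visit 1 falls, so U is an assumption and its whole range is shown. Each woman's cycle length is taken as constant.

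Formulas:

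- Start of third course = U + 2L.
- Last dosing day of third course = U + 2L + 6.
- Dosing passes day 90 when U > 84 − 2L. The course starts after day 90 when U > 90 − 2L.
- If U is uniform over the cycle, the share dosed after day 90 is (L − (84 − 2L))/L = (3L − 84)/L, and the share starting after day 90 is (3L − 90)/L. Negative values are set to 0.

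| L (days) | Last dosing day, U = 0 to U = L | Share dosed after day 90 | Share starting after day 90 |
|---|---|---|---|
| 21 | 48 to 69 | 0% | 0% |
| 28 | 62 to 90 | 0% | 0% |
| 29 | 64 to 93 | 3/29 = 10% | 0% |
| 30 | 66 to 96 | 6/30 = 20% | 0% |
| 32 | 70 to 102 | 12/32 = 38% | 6/32 = 19% |
| 35 | 76 to 111 | 21/35 = 60% | 15/35 = 43% |

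The overrun therefore needs two things: a cycle longer than 28 days, and a first on-study menses late enough after visit 1. At L = 35 the wait must exceed 84 − 70 = 14 days; at L = 30 it must exceed 84 − 60 = 24 days. The latest possible dosing day is 35 + 70 + 6 = 111.

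**Step 3: effect of the two added visits.** Assessment at days 120 and 150 restores 5 of 5 visits. The latest dosing day, about 111, then falls before a scheduled assessment at day 120.

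**Step 4: the end-of-treatment statements.** Study Procedure attaches completion of active treatment to day 150, whereas Laboratory Tests puts the end of treatment at day 90. Read literally, the first would place both unticked visits within the treatment period.

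**The case against.** The strongest reply is that this is a mismatch between text and table whose consequences are uncertain. A reader might infer that late reactions will be missed and comparator reactions under-counted. The documents do not support that as a statement of fact, for four reasons.

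- Two text sections set the wider duty. Nothing says that staff at this single-site trial follow Table 2 over the text, and the CRFs are not shown.
- Cover at days 120 and 150 is not nil. Table 2 keeps signs and symptoms at both visits, and the section on prior and concomitant medication has participants asked to report unusual occurrences promptly.
- The imbalance between arms is conditional. It needs cycles longer than 28 days and a suitable timing of visit 1. If U = 0, even a 35-day cycle finishes the third course at day 76. It also takes treatment-group dosing to end at about day 90, which the day-150 label contradicts.
- The table speaks of adverse drug reactions and the text of adverse events. The table row ends at the same visit as drug compliance, which suggests an on-treatment check.

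The first three points stand as limits on the claim. The fourth does not remove the conflict, because Table 2 has no separate adverse-event row: the requirement in the safety text appears nowhere else in the schedule. Nor are signs-and-symptoms checks and unprompted reports equivalent to scheduled adverse-event assessment in an open-label comparison.

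**Conclusion.** The contradiction is in the current text and needs no outside source. If Table 2 is followed, adverse events are not systematically assessed at 2 of 5 follow-up visits, the last 60 of 150 days, with partial cover from other procedures.

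The gap may include control-group treatment time: 0% of women at cycles of 28 days or less, rising to 60% at the longest eligible cycle, on the assumption that U is uniform. The 60% is the extreme of the eligible range, not a trial-wide estimate. The documents give no distribution of cycle lengths, so the overall share is unknown, and without adverse-event rates so is the number of events affected. The cut-off could fall unequally on the arms, but this is a possibility and not a demonstrated bias. No efficacy outcome, sample size or test is affected.

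**What to change.** - In Table 2, tick adverse-event assessment at day 120 (visit 5) and day 150 (visit 6), to agree with Safety Outcomes and Data Safety and Monitoring.
- Record the date of the last trial dose for each participant, and report adverse events by arm over the full 150 days, so that events on and after treatment can be told apart.
- Reconcile the Study Procedure label at day 150 with the day-90 end of treatment in Laboratory Tests. Which is intended is for the sponsor to state.

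The cost is one extra CRF page at two visits that already take place, with no new visits, tests or participants. As 79 women had been enrolled by December 2024, the correction should be made promptly, and the report should say if earlier participants were assessed only to day 90.
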